**Fig. 2 Fig2:**
[figure not shown]
Study Design

#### Setting and procedures

The study will take place through selected sites of a pre-existing system of community-based safety programs for farm and rural youth (Progressive Agriculture Safety Day). Local Safety Day programs will serve as clusters.

#### Subject sample

Farm and rural youth, as well as Safety Day instructors and coordinators will be sampled. Inclusion criteria for youth participants include enrollment in grade 4, parental consent, English speaking, and attending a Safety Day event included in the cluster sampling. Inclusion criteria for coordinators include demonstrated ability to successfully coordinate a Safety Day program, interest in the study, opportunity to implement the lesson in the designated study period, and willingness to comply with study procedures. Site selection will be aimed at including a diverse study sample, from the perspective of race, ethnicity, and geography. Inclusion criteria for instructors include accepting a hearing health teaching assignment at a Safety Day event included in the cluster sampling.

#### Recruitment

The study will use pre-existing Safety Day protocols for recruitment and consenting participants, with some modifications. Local Safety Day programs from diverse areas across the US will be offered the opportunity to enroll by a member of the study team. Recruitment of Safety Day instructors will be done in collaboration with the study team, who will collaboratively develop instructor recruitment strategies. Coordinators (and delegates) will recruit youth to participate.

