**Methods:**

The purpose of this project is to test innovative hearing health education programs delivered to a large target group and to determine the effectiveness and sustainability of these programs in promoting hearing health among farm and rural youth. Specifically, this project includes: a) an interactive face-to-face informational program alone, b) an interactive face-to-face informational program followed by an Internet-based booster, and c) a no-intervention control. Sites will include selected affiliates of a major farm youth safety education organization. Data will be collected at baseline, 3, and 12 months. A linear mixed model will be used to compare the effectiveness of the three interventions over time. Descriptive statistics will be used to compare program costs and sustainability ratings.

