### Interventions

The study aims to test alternative hearing health education programs, and determine their effectiveness and sustainability for farm and rural youth.

Intervention A consists of the interactive face-to-face hearing conservation program developed by the project team. It consists of discovery-based, developmentally appropriate activities designed to teach common farm and recreational sources of hazardous noise, effects of hazardous noise on ear structure and function, and age-appropriate ways to protect oneself, e.g., walk away, turn it down, and wear protection. The 20-minute lesson includes student involvement in demonstrations and visuals, demonstration and supervised practice in insertion of a child-safe hearing protection device, provision of a sample hearing protector, and elements relevant to the rural and farm community (e.g., common farm noise sources). In a preliminary test with 64 fourth grade students, comparison of pre- and post-test results showed changes of scores in the desired direction, and pre-post-test differences were statistically significant*.* In addition, results of the pilot test suggested that overall, the pilot program was acceptable to school officials and students, instruments were reliable and valid, and the brief educational program is feasible.

Training in use of the face-to-face hearing health lesson plan will be provided to selected local safety program coordinators through face-to-face and virtual train-the-trainer sessions conducted by study personnel, and a written lesson plan; the Study Coordinator will also reach out to instructors by offering individualized training and consultation. Coordinators will prepare instructors, include the lesson in their local program, and complete surveys. The hearing health lesson includes use of easily accessible teaching materials, e.g., paper-based visual aids, locally-sourced noisy equipment (e.g. electric leaf blower), pipe cleaners, and a sound meter.

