#### Randomization

To reduce contamination of intervention effects across participants, randomization will occur at the level of local Safety Day programs. Participating Safety Day programs will then be randomly assigned to one of the three study conditions so that individuals within the same site receive the same intervention.

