#### Intervention effectiveness evaluation

After obtaining parental informed consent and soliciting the assent of child participants, pre- and post-intervention data will be collected from youths. Pre-test data will be collected via pencil-and-paper survey forms prior to the delivery of content. Three- and 12-month post-test data will be collected via the youth’s preferred communication medium following the booster intervention. Instrument means, standard deviations, and alpha coefficients are summarized in Table 2.

**Table 2 Tab2:** Timetable of project activities and benchmarks for success

Activity	Year 1 months						Year 2 months						Year 3 months						Year 4 months		
	1/2	3/4	5/6	7/8	9/10	11/12	13/14	15/16	17/18	19/20	21/22	23/24	25/26	27/28	29/30	31/32	33/34	35/36	37/38	39/40	41/42
Recruit, enroll & randomize 36 sites	X	X	X	X																	
Train coordinators (Groups A,B); & distribute materials (Groups A,B,C)		X	X	X	X	X															
Recruit 24 instructors; enroll youth; collect baseline data; deliver interactive program (Groups A,B)					X	X	X	X													
Distribute, collect 3-month surveys (Groups A,B)					X	X	X	X	X	X											
Distribute booster reminders (Group B)							X	X	X	X	X	X									
Collect 12-month surveys; distribute incentives (Groups A,B,C)											X	X	X	X	X	X					
Complete sustainability assessment														X							
Analyze data															X	X	X				
Submit progress reports						X						X						X			X
Disseminate & submit manuscripts																			X	X	X

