### Study challenges and proposed solutions

#### Child participation

The study procedures include measures to protect children from coercion. Parental consent will be obtained prior to data collection; children who are not enrolled in the study will also receive the Safety Day intervention, but no data will be collected from them. Safety Day personnel are well-known local community members who are invested in the health and safety of youth in their own community, and often have a history of volunteering with the program for many years.

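### Youth are recruited after site randomization by coordinators who know intervention from control, and the stated model does not remove a resulting baseline gap in intention

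*Protocol article*

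**What the plan says.** All places are in the protocol article.

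- **Unit of allocation.** Randomization: "randomization will occur at the level of local Safety Day programs".
- **Order of events (Table 2).** "Recruit, enroll & randomize 36 sites" is marked for months 1-8. The row "Train coordinators (Groups A,B); & distribute materials (Groups A,B,C" is marked for months 3-12, with training for A and B only. The row that contains youth enrollment and baseline data, "Recruit 24 instructors; enroll youth; collect baseline data; deliver interactive program (Groups A,B", is marked for months 9-16.
- **Who recruits.** Recruitment: "Coordinators (and delegates) will recruit youth to participate". Existing local procedures are used, with modifications that the article does not describe.
- **What coordinators do in A and B.** Interventions: "Coordinators will prepare instructors, include the lesson in their local program, and complete surveys". Group C is "a no-intervention control" (abstract, Methods).
- **Consent.** Parental consent is an inclusion criterion (Subject sample). Under Child participation, "children who are not enrolled in the study will also receive the Safety Day intervention", but no data are collected from them.
- **Model.** Statistical analysis names intervention type as the main fixed effect, demographic variables as further fixed effects and a random intercept for site. The Demographics section lists sex, age and race/ethnicity. Baseline intention is not named as a covariate, and no treatment-by-time term is written out.

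**The concern.** Randomizing sites makes the sites comparable in expectation. It does not make the consenting youth comparable when consent is sought after allocation by someone who knows the arm. A coordinator trained in a hearing lesson may present the study differently, or to different families, from a coordinator at a control site. The analyzed groups could then differ in intention to use hearing conservation strategies, the primary measure, before anything is delivered. If the model carries that difference into the tested intervention effect, the trial may credit the programs with an effect they do not have, or hide one that they do have.

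**Working it through.** **1. Order and knowledge of arm.** Site randomization ends in month 8 and youth enrollment starts in month 9, so on this timetable every child is enrolled after the arm is fixed. With 36 sites divided equally, each arm has 36/3 = 12 sites. The 24 planned instructors match the 2 x 12 = 24 sites in A and B. Coordinators there are trained and prepare instructors, while control sites have no lesson. Coordinators must therefore know A/B from C, which is the main Aim 1 comparison. The article does not say whether they know A from B at enrollment.

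**2. The plan's own power figure.** Inputs from Power and sample size justification: d = .48, ICC = .10, 16 youth per site, two-sided alpha .05, 12 v 12 sites for one intervention against control.

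- SE = sqrt[4 x (.10 + .90/16)/24] = sqrt[4 x .15625/24] = .161 SD.
- Noncentrality = .48/.1614 = 2.97. On 22 df, power is 81.1%, against 80% stated. The figure reproduces.

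**3. Size of a recruitment gap (assumed; the article gives no consent rate).** Let consent depend on a latent normal score correlated rho with standardized intention. With consent rate p and z the matching normal cut-off, mean intention among consenters is rho x phi(z)/p.

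| Scenario | Calculation | Gap for rho = .1 / .2 / .3 |
|---|---|---|
| 50% consent, selection in intervention sites only | rho x .399/.5 = .798 rho | .08 / .16 / .24 SD |
| Same rho in all arms, consent 40% v 60% | (.966 - .644) rho = .322 rho | .03 / .06 / .10 SD |

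In the first scenario with positive rho, intention is higher in the intervention arms. In the second, the arm with the **higher** consent rate has the **lower** mean intention. If trained coordinators recruit more successfully, the gap then runs against the programs.

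**4. What the stated model does with a gap g.** Suppose g persists, and the true effects are e3 and e12 at 3 and 12 months. Weight the occasions equally.

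- Baseline as a repeated outcome, main effect of intervention only: [g + (g + e3) + (g + e12)]/3 = g + (e3 + e12)/3. The whole gap enters.
- Follow-up outcomes only, demographics as covariates: [(g + e3) + (g + e12)]/2 = g + (e3 + e12)/2. The whole gap enters again, except for any part that demographics explain.
- Contrast from baseline: (g + e3) - g = e3. A stable gap cancels.

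**5. Consequence for the test.** The SE is that of step 2. There is no true effect, and a gap b is carried in full into a single-occasion comparison.

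| b (SD) | Share of .48 | Rejection rate (nominal 5%) |
|---|---|---|
| .05 | 10% | 6.0% |
| .10 | 21% | 9.1% |
| .15 | 31% | 14.4% |
| .20 | 42% | 22.0% |
| .25 | 52% | 31.7% |

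With 12.8 youth per site (16 less 20%), the rates at .10 and .20 are 8.8% and 20.6%.

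**The case against.** **Consent is not the gate to the lesson.** A reader might infer that A and B families gain the program by consenting while control families gain only surveys. The Child participation section does not support this: children who are not enrolled also receive the lesson. In Group A, as in control, consent covers data collection only; Group B's later booster is the one place where the offer might differ. This weakens the mechanism. It does not remove it, because consent decides who is analyzed and the recruiter still knows the arm.

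**Baseline is measured.** Intention is recorded before the content is delivered, the abstract speaks of comparison over time, and Statistical analysis refers to improvement relative to control. A stable offset cancels from an improvement contrast, so the step 3 gaps are baseline differences and not bias in such a contrast. This stands as far as it goes. However, the means by time and treatment are described as descriptive follow-up to a significant result, and the effect named for testing is intervention type.

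**The sizes are assumed.** This stands in full. A gap of .24 SD, half of the target effect, needs a correlation of .3 in intervention sites and none in control sites.

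**An article condenses the protocol.** The full document may hold common invitation and consent wording, and its absence here is no evidence of arm-specific invitations. The point rests on what the article does state: the order, the recruiter and the model terms. Fixed eligibility criteria and the coordinator survey of recruitment procedures are partial safeguards.

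**Conclusion.** The design leaves room for the consenting youth to differ between intervention and control arms before any intervention, and the analysis as described does not take a baseline gap in intention out of the tested effect. This is a risk, not a demonstrated imbalance. Under the assumptions shown, the gap is roughly .03 to .24 SD. Across the tabulated .05 to .25 SD, the 5% test rejects 6.0% to 31.7% of the time with no true effect, if the gap persists in full and no baseline contrast is taken.

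A reader might conclude that recruitment will inflate the programs' effect. The documents do not support a direction: with equal selection and unequal consent, the arm that recruits more has lower intention, and a true effect would be understated. The stated 80% power is not in question here.

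**What to change.** 1. Use the same arm-neutral invitation and parental consent text at all 36 sites, for all eligible grade-4 attendees. Because Group B youth have their time on the booster website tracked (Process evaluation), the text has to cover that possibility for everyone.
2. Do not tell families the arm until consent and the baseline survey are complete.
3. Estimate the primary intervention effect on 3- and 12-month intention adjusted for baseline intention, or as a treatment-by-time contrast from baseline. Report baseline intention, and eligible and consented numbers, by arm.

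The cost is a slightly longer consent text and a simple count at each site. Baseline intention is already collected, and the sample size does not change. Two limits remain: coordinators cannot be masked to A/B against C, and baseline adjustment does not remove unmeasured differences in motivation. Steps 1 and 2 are therefore needed as well as step 3.

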#### Retention

With parental consent, youth will select their preferred communication media (telephone, postal, email), which will be used to communicate study activity reminders and surveys. The study coordinator will distribute reminders, and 3- and 12-month follow-up surveys by email, postal mail, or phone. Coordinators will access youth for 12 month follow-up as they return for Safety Day participation in the subsequent yearly meeting. The study team will support the PAF Safety Day trainers, coordinators, and instructors through site visits and frequent email and telephone contacts. Participating youth will be recognized with a $5 cash incentive for completing up to three (depending on study arm) surveys. Coordinators will be awarded checks on submission of study materials (surveys) as tokens of appreciation for their contribution to accomplishment of study goals (e.g., completion of training, coordination, & teaching; responding to survey requests).

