#### Self-reported measures

The study effectiveness measures are based on participant self-report, which is vulnerable to social desirability bias. However, in a nationwide sample of farmers participating in a test of hearing conservation interventions, participants scored low on a standard measure of social desirability reporting.^81^ In other reports, self-report and observations were highly correlated [42, 43].

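### Telephone follow-up of the self-reported primary outcome runs through the coordinator who coaches Group A and B instructors, so a phone caller would know the arm

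*Protocol article*

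**What the plan says.** All places are in the protocol article.

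- **Retention** gives the follow-up surveys to one role: "The study coordinator will distribute reminders, and 3- and 12-month follow-up surveys by email, postal mail, or phone". The child chooses the route: "youth will select their preferred communication media (telephone, postal, email), which will be used to communicate study activity reminders and surveys".
- **Intervention effectiveness evaluation** makes that route the means of data collection, not only of reminders: "Three- and 12-month post-test data will be collected via the youth’s preferred communication medium following the booster intervention". Baseline differs: "Pre-test data will be collected via pencil-and-paper survey forms prior to the delivery of content".
- **Interventions** gives the same role a part in delivering the lesson: "the Study Coordinator will also reach out to instructors by offering individualized training and consultation". Table 2 shows which arms are trained: "Train coordinators (Groups A,B); & distribute materials (Groups A,B,C").
- **Retention** adds a second route at 12 months: "Coordinators will access youth for 12 month follow-up as they return for Safety Day participation in the subsequent yearly meeting".
- **Statistical analysis** makes the 6-item intention scale the primary measure and compares each intervention with the no-intervention control.
- **Self-reported measures** accepts that self-report is open to social desirability bias. It answers first that "in a nationwide sample of farmers participating in a test of hearing conservation interventions, participants scored low on a standard measure of social desirability reporting", and then that self-report and observation agreed closely in other reports.

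**The concern.** The children and instructors cannot be blinded to a lesson, but the person who collects the answers can be. As the article assigns the roles, a child who picks the telephone would be surveyed through someone who has helped prepare the lesson in Groups A and B and so knows which sites received it. The sample item of the intention scale asks whether the child would use earplugs, which is behaviour the lesson teaches.

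Randomisation does not protect against this, because the influence arises after allocation. An interviewer effect that was equal in all arms would cancel. One that depends on the caller knowing the arm, or on a taught child answering aloud to a project adult, would not. It would add to the apparent effect of A and B against C on the primary outcome, and could not be reliably separated from a real effect afterwards.

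The article's two reassurances do not reach this case. The first concerns farmers, whereas the trial enrols grade 4 children. The second can support reported behaviour, which is one of the measures, but an intention cannot be checked by observation. Neither deals with who collects the answers.

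**Working it through.** **Step 1. Does the text put an arm-aware person on the phone route?**

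1. Telephone is an allowed medium, and post-test data come through the chosen medium (Retention; Intervention effectiveness evaluation).
2. The study coordinator distributes the surveys (Retention).
3. The study coordinator coaches lesson instructors (Interventions), and training takes place in Groups A and B only (Table 2).
4. So the role that handles phone surveys knows which sites have the lesson. This follows from what is stated, not from a detail left out.

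**Step 2. Reproduce the plan's power, to obtain a standard error.** Inputs from Power and sample size justification: d = 0.48, ICC = 0.10, 36 sites in three equal arms (J = 12 per arm), m = 16 per site, alpha 0.05 two-sided.

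- Design effect = 1 + (16 − 1) × 0.10 = 2.5
- SE(d) = √(2 × 2.5 / (12 × 16)) = √(5/192) = 0.161 SD
- Noncentrality = 0.48 / 0.161 = 2.97. The noncentral t with 2 × 12 − 2 = 22 df gives power 81.1%, against the stated 80%. The plan's figure is reproduced.

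**Step 3. What an interviewer shift would do.** Let p be the share answering by phone (taken as equal in the two arms) and s the extra shift, in SD, of phone answers in an intervention arm compared with control. Then

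- bias in the contrast = p × s
- type I error under a true null = two-sided rejection rate of the noncentral t (22 df) with noncentrality (p × s) / 0.161

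The article gives neither p nor s. Every value below is an assumption.

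| p | s (SD) | bias (SD) | type I error |
|---|---|---|---|
| 10% | 0.1 | 0.01 | 5.0% |
| 25% | 0.2 | 0.05 | 6.0% |
| 50% | 0.2 | 0.10 | 9.1% |
| 50% | 0.3 | 0.15 | 14.4% |
| 40% | 0.4 | 0.16 | 15.8% |

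The calculation treats the comparison as a t-test on clusters at one time point. The planned mixed model with demographic covariates would have a somewhat different standard error, so the percentages are indicative.

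**Step 4. At which visit?** Table 2 lists 3-month surveys for Groups A and B only, while Statistical analysis has all individuals measured at 3 months. If Table 2 is right, there is no 3-month contrast with C to be biased, and the point bears on the 12-month contrast. At 12 months some answers may come through local coordinators at the next Safety Day. That could lower the phone share, but those coordinators also know what their own site taught.

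**The case against.** **No passage says that items are read aloud.** The coordinator distributes surveys, Process and outcome measures says students complete them, and reading grade levels are reported, as suits instruments that a child reads. This stands in part: asking by phone is an inference, though the natural one when answers are collected by telephone. Email and post involve no interviewer.

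**Scripts and masking of callers belong in the full protocol or a field manual.** Their absence from the article is indeed no finding. The overlap of roles, however, is stated in the article, and the point rests on that alone.

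**Taught children can repeat the expected answer on paper too.** This stands. That part of social desirability comes with any self-report after education, which the article acknowledges, and no change of caller removes it. Only the added effect of an interviewer belongs to this point.

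**A reader might infer that the move from paper at baseline to phone at follow-up itself biases the comparison.** The documents do not support that. All arms start on paper, Aim 1 compares arms, and a mode change common to all arms cancels.

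**Telephone is offered to keep children in the study.** This also stands. The design already allows for 20% missing post-test data, and barring phone answers could add to it. Retention also has the study team as a whole supporting sites, including by site visits, so a fully masked caller may not exist.

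**Conclusion.** The point holds as a risk that the stated role assignment creates: phone answers to the primary outcome would pass through someone who knows the arm, and the article's reassurance does not cover children's stated intention. The plausible direction favours A and B over C, but it is not shown.

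A reader might go further and infer that some definite share of the planned effect of 0.48 would be bias. The documents do not support any such figure: the phone share and the shift are both unknown, and their product can be close to zero. Under the assumptions above, the result runs from no visible change in type I error (10% by phone, 0.1 SD) to about 16% (40% by phone, 0.4 SD). The conclusion also assumes that phone surveys are asked by the coordinator in person and that the full protocol contains no safeguard. The case for acting is that the safeguards are cheap and must be in place before the follow-up surveys start.

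**What to change.** Keep the phone as an option, and amend Retention and Intervention effectiveness evaluation as follows.

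1. In every arm, offer the self-completed form (post or web link) first. Use the phone for contact and reminders, and for answers only where the child would otherwise not respond.
2. Where answers are taken by phone, read a fixed script word for word. As far as existing staffing allows, the caller should be a team member who does not support the A and B sites and is not shown the arm.
3. Collect 12-month answers at the next Safety Day as self-completed forms too, not by local staff asking the questions.
4. Record the mode of every survey. Add a sensitivity analysis of the primary outcome, either limited to self-completed surveys or with an arm-by-mode term. Mode is chosen and not randomised, so this analysis can expose a problem but cannot fully correct it.

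The cost is some reassignment of existing staff, plus a few extra reminders or lost responses among children who would have preferred the phone. Design, sample size and outcome are unchanged.
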